## Discussion

Trauma or major surgery go along with initiation of pro-inflammatory cascades leading to a variably pronounced SIRS [41]. Severity of SIRS (next to patient-specific variables) depends on the type, site, invasiveness, and duration of the performed procedure with an incidence of up to 60% after major surgery [42]. Inflammatory intestinal dysfunction, characterized by gastrointestinal motility disorder and a breakdown of intestinal barrier, appears to be a major prognostic factor. No preventive or directed treatment exists [5, 6].

Beside the pioneering work of Tracey et al., multiple other studies in rodents demonstrated the beneficial effects of CAIP activation via VNS before LPS challenge in the last years. For example, Zhou and co-workers showed a reduced cytokine release and a prevention of intestinal tight junction breakdown with a reduced bacterial translocation after LPS application and VNS. Our group as well as Huston and co-workers demonstrated beneficial effects of VNS in rodent LPS models with reduced cytokine liberation and an improved survival [15, 30]. In humans, there is growing evidence that a reduced vagal tone is associated with an increased morbidity and mortality after surgery-related SIRS or sepsis [43, 44]. It seems obvious that prophylactic stimulation of the vagal tone and thereby the CAIP might mitigate postsurgical morbidity related to postoperative inflammation. However, clinical trials investigating the prophylactic effect of VNS in acute postoperative inflammation in humans are lacking. As the occurrence and severity of postoperative SIRS vary greatly depending on various factors and cannot be predicted, a randomized controlled trial investigating SIRS prophylaxis using VNS requires a large sample size with an associated high financial burden. To avoid the required large sample size due to unpredictable SIRS occurrence, a reproducible and standardized model mimicking a systemic inflammation as it occurs during SIRS was expected to be helpful for a pilot trial. We therefore established the present study protocol to investigate the potential prophylactic effects of taVNS in a model of systemic inflammation.

### LPS challenge to induce a standardized systemic inflammation

To induce a standardized and reproducible SIRS, LPS challenge will be performed. The use of LPS to cause experimental systemic inflammation has been extensively investigated, showing no severe or long-term adverse effects [34]. Administration of LPS at a dosage of 2 ng/kg bodyweight induces specific physiologic and metabolic processes comparable to SIRS with culmination of symptoms after approximately 2 h, making it an ideal model to investigate potential prophylactic or therapeutic tools in systemic inflammation [45]. In the literature, dosing of LPS varies between 0.2 and 4 ng/kg bodyweight in human studies. We decided to administer LPS at this dosage since it is the most used and has been shown to induce distinguished symptoms of systemic inflammation with only minimal and tolerable side effects. The crucial difference to actual SIRS lies in the complete reversibility of symptoms after 6–8 h and the absence of secondary health damages [46–48].

Of note, LPS challenge leads to symptoms of SIRS, which might cause greater discomfort to individual participants. If subjects suffer from these symptoms during the trial, paracetamol can be administered at any given time, ameliorating these symptoms. In these participants, a potential interaction with the systemic inflammatory response needs to be considered during later analysis.

To achieve the highest level of safety, all participants are monitored with an ECG, blood pressure and peripheral blood oxygenation during the trial. Of course, proper pre-interventional information, consent of the participants, a thorough examination, and history-taking are mandatory before inclusion into the study. To evaluate SIRS-related symptoms and the inflammatory extent of LPS administration, a clinical score in conjunction with vital parameters as well as inflammatory cytokines in patient’s sera will be used. This triad of variables has been used in a plethora of clinical trials and is well-validated as a diagnostic tool to describe LPS-related SIRS [37–39]. A potential amelioration of the inflammatory extent of LPS administration through CAIP activation via VNS can be displayed.

### taVNS for activation of the CAIP

Electrical stimulation of the VN is usually accomplished by implanting a stimulation electrode near the cervical VN. However, to use VNS as a prophylaxis, a surgical procedure under general anesthesia before SIRS inducing surgery would be mandatory to implant the stimulation electrode in proximity to the cervical neurovascular bundle (carotid artery, jugular vein, VN). Furthermore, the electrode as well as the stimulator needs to be explanted after its use, necessitating another procedure. Considering possible surgical complications associated with electrode implantation and explantation, treatment of postoperative SIRS using iVNS seems infeasible.

Kox and colleagues thought of a model of cervical VNS using a special stimulation catheter placed in the jugular vein near the VN. The idea behind the intravenous stimulation is extremely interesting because during more invasive surgical procedures patients usually require a central venous line anyway. Therefore, using the transvenous stimulation catheter, prophylactic stimulation would be possible without exerting unnecessary harm to patients beyond a cervical venous puncture. In the trial, after placement of the stimulation catheter and VNS, participants underwent LPS challenge. Surprisingly, no anti-inflammatory effects of jugular VNS in terms of reduction of symptoms or cytokines in participants sera were seen [39]. The actual reason behind the missing anti-inflammatory effect of transvenous VNS is not yet understood. It is arguable that only efferent fibers of the VN were activated and that the stimulation was not strong enough possibly reducing a potential anti-inflammatory effect. Kox and colleagues later argued that different ways of VNS need to be investigated with emphasis on non-invasive auricular VNS with stimulation of afferent vagal fibers necessitating central nervous interconnection, potentially enhancing anti-inflammatory effects [37].

Technical progress within the last years led to the development of a device for taVNS. Interestingly, functional MRI studies could verify that taVNS via ABVN led to an activation of the same brain areas as iVNS suggesting comparable effects [22]. Avoiding risks associated with surgical implantation of a stimulation electrode for iVNS and taVNS allows for non-invasive stimulation of the VN. The afferent branch of the VN innervating the concha auricularis (ABVN) is stimulated transcutaneously with electrical impulses applied via electrodes connected to a handheld stimulation device sized comparable to a smartphone (Fig. 1). The ABVN then projects to the NTS leading to activation of a complex neuronal network lastly resulting in activation of the dorsal motor nucleus [22]. As demonstrated before, stimulation will commence at 0.1 mA and will be increased until the participant perceives a tingling sensation. Further increase of intensity will define the threshold when the sensation becomes discomforting. The intensity will stay below this threshold. The optimal intensity varies between 0.3 and 0.8 mA [21, 49, 50]. Recent research has shown that setting the stimulation threshold just below the verge of a tingling sensation, becoming painful at the outer ear, is strongly correlated with activation of the vagal nerve, as shown, for instance, in changes in heart rate variability [51]. It currently is the most standardized and reproducible modus operandi in taVNS. It is hypothesized that a tingling sensation is necessary because taVNS below a painful threshold should recruit myelinated auricular Aβ fibers responsible for cutaneous touch sensation and fibers responsible for central activation of vagal nuclei instead of myelinated Aδ fibers for cutaneous nociception [52].

Several trials were able to show that not only iVNS dampens inflammatory reactions, but also taVNS leads to decreased serum levels of IL 1β, IL 6, TNF-α, and HMGB-1 in patients with myocardial infarction or atrial fibrillation compared to sham-stimulated controls. These results indicate a close relation of vagal tone and immune response [25, 31, 32, 53]. However, there are no existing trials investigating the prophylactic use of taVNS before activation of an inflammatory cascade. Considering the interesting results of CAIP activation in animal models, a prophylactic stimulation before beginning of an inflammatory stimulus appears to be the key to successful abrogation of inflammation [14, 54]. This finding is supported by a recent study of Kox and colleagues demonstrating the efficacy of the acetylcholine receptor agonist and CAIP activator GTS-21 antecedent to LPS stimulation leading to a decrease in pro-inflammatory cytokines in healthy subjects [38]. Irrespective of the catalysator of the inflammatory reaction (surgery, trauma) and its associated risks, taVNS allows for harmless CAIP activation at any time, even in a preventive setting [55].

A great advantage of taVNS is that only few and minor side effects have been described and they mostly occur only during long term stimulation. For example, in the treatment of epilepsy, it was rarely associated with local side effects at the site of stimulation like itching, dysesthesias, rash, and other skin-related symptoms. Single cases of interference with the autonomic nervous system like headache, nausea, vertigo, bradycardia, or bronchoconstriction have also been described [56–59]. To ensure highest safety levels, the NeuroSIRS-Study will be performed at the Phase I trial unit of the University Hospital of Bonn, with participants being under continuous monitoring and always supervised by a physician. In case of unexpected severe side effect and emergency, a team of experienced physicians of the intensive care unit are readily available.

To date, only one exploratory clinical trial was able to show anti-inflammatory properties of perioperative taVNS in patients undergoing thoracic surgery showing a decline in IL 6 levels and infectious complications postoperatively. Putative intestinal effects were not studied [60]. In addition to this, Chapman and colleagues recently demonstrated in a pilot study with a small case number a reduced time to first flatus and faster solid food tolerance after colorectal surgery preceded by transcutaneous cervical VNS (stimulation of the efferent branches of the VN, no stimulation of the ABVN) compared to a sham-stimulated control group. The trial firstly described a motility-enhancing effect of non-invasive VNS postoperatively; unfortunately, inflammatory markers were not investigated [61].

Considering data from animal models showing the anti-inflammatory and motility-enhancing effects of taVNS, current knowledge about the association of vagal tone and outcome after SIRS and first trials investigating taVNS during lung or colorectal surgery, a clinical trial to investigate taVNS as a prophylactic treatment for SIRS and SIRS-related disruption of intestinal viability seems to be mandatory and consequent.

### Assessment of intestinal motility and barrier integrity

Intestinal viability will be evaluated using a composite analysis of intestinal motility and integrity of intestinal barrier function. At first, intestinal motility during systemic inflammation will be investigated using the SmartPill®. The SmartPill® has already been widely used to assess intestinal peristalsis in patients with impaired intestinal motility such as diabetic gastropathy or chronic constipation. We recently conducted a clinical trial demonstrating the safety of the SmartPill® in patients undergoing abdominal surgery, acquiring first objectifiable data on postoperative ileus [35]. To our knowledge, there is no parameter or biomarker to measure impairment of intestinal motility during SIRS-associated paralytic ileus. As the reduced perfusion followed by lack of peristalsis is the initial step of intestinal failure which finally leads to bacterial overgrowth and translocation, we hypothesize that the SmartPill® will be of great value to deliver objectifiable, reproducible data concerning the impairment of gastrointestinal motility in our standardized SIRS model. Lack of peristalsis in combination with impaired intestinal perfusion due to hypotension results in stasis, bacterial overgrowth, and finally the breakdown of intestinal barrier function with bacterial translocation and abdominal sepsis. This pathophysiological cascade led to the idea that the gut is the motor of critical illness [6]. Therefore, improving not only peristalsis but also the maintenance of barrier function would be a crucial step in SIRS prophylaxis. As it was shown in a rodent model, taVNS is able to prevent LPS-induced intestinal barrier breakdown resulting in a diminished bacterial translocation [15].

Integrity of the intestinal barrier will be investigated via analysis of the lactulose/mannitol ratio in participant’s urine. Urinary excretion of the two orally administered non-metabolizable sugars, lactulose and mannitol, is a valuable marker for evaluating intestinal permeability. While mannitol, a sugar monomer, is absorbed trans-cellular, lactulose, a dimer, is absorbed to a lesser extent and therefore marks mucosal integrity. We chose this model due to its non-invasive, easy-to-use nature and, to our knowledge, no known interactions between the sugars and the immune response. The test has been used in a variety of different indications and is a sensitive parameter to assess intestinal health [62].

### Limitations of the NeuroSIRS-Study

Our study offers several opportunities but has also some limitations. Small sample size might be considered as a possible limitation of the NeuroSIRS-Study. Nevertheless, it is a pilot study and designed to acquire first data concerning the influence of prophylactic taVNS on systemic inflammation in a highly standardized model. To induce systemic inflammation, LPS challenge is used. Notably, intravenous administration of LPS only leads to activation of a single toll-like receptor, while postoperative SIRS originates from a variety of inflammatory stimuli [34]. It might be argued that LPS challenge only partially mimics postoperative inflammation and is an artificial model not reflecting clinical reality. Even so, the LPS challenge remains the most used, ethically acceptable, and well-established strategy to systematically investigate SIRS and potential treatments in a standardized and reproducible manner.

Another crucial point is the side effects associated with LPS administration and dosage. Errors in dosing and dilution must be avoided to prevent severe side effects and potential harm to participants. Usage of LPS has been approved by the local ethics committee as it is the most standardized and safest way to induce systemic inflammation in an experimental setting. Nevertheless, even at a dosage of 2 ng/kg bodyweight, potent symptoms of SIRS are to be expected. Comparable to a “flu-like” infection, body temperature is expected rise above 38 °C; shivering and fatigue may occur. Hypothetically, allergic reactions towards LPS are possible but rather unlikely considering that the substance is highly purified and processed under “good manufacturing process” conditions by a certified institution. Since individual case reports on LPS-induced bradycardia exist, patients with a history of vagal reactions or pre-existent bradycardia are excluded from the study [63, 64]. If symptoms of inflammation are experienced strongly, paracetamol can be administered to weaken these symptoms. Consecutively, recruitment, an issue in every clinical trial, could be challenging due to the likely side effects. However, to guarantee the highest safety levels, the NeuroSIRS-Study will be performed at the Phase I trial unit of the University Hospital of Bonn with a medical emergency team in reach within few minutes.

Only healthy, Caucasian men are included into the trial, unrepresentative of the heterogenous surgical population [65]. It has been demonstrated that LPS-induced inflammatory responses vary between individuals of African vs. European ancestry with a lower inflammatory response in those of African descent [66]. Furthermore, specific differences in the (neuro)-immune and neuroendocrine inflammatory response between men and women have been described. To exclude potential intersexual and interracial differences in immunologic and endocrine response to LPS challenge [67, 68], we accepted this flaw in study design, owing to the exploratory nature of the trial. Of note, due to endotoxin tolerance persisting for an unknown time period, participants who previously underwent endotoxin challenge will be excluded from the study [34].

During the trial, the SmartPill® is used to investigate intestinal motility during SIRS. To generate valid data on specific transit times, changes in gastrointestinal pH measured by the capsule are necessary. It should be noted that pH is highly influenced by VN activation through regulation of secretion of hydrochloric acid [69]. While transit from the stomach to the duodenum is usually well visible, passing of Bauhin’s valve might be hard to detect due to only minimal physiologic changes of 1–2 points in pH value. This would result in difficulties in read out of small bowel and large bowel transit times. However, all other parameters (gastric emptying, whole gut transit, peristaltic activity) measured by the SmartPill® can be analyzed without any issues.

During taVNS a tingling sensation at the outer ear is described, which is not felt during sham stimulation, leading to a potential unblinding during the trial. This problem will be solved during participant education, mentioning that certain sensations might be felt intermediately but are not mandatory. Furthermore, randomization, setting, and placement of the electrode are performed by personnel not further involved in participant care or data extraction/analysis.

Finally, we believe that despite the limitations, the LPS challenge is a suitable and well-controlled approach to mimic postoperative SIRS to ensure reproducible results that allows investigation of the immune modulatory actions of taVNS in humans under inflammatory conditions.

In conclusion, the present study aims to give insight into use of taVNS in humans in a standardized and reproducible model of systemic inflammation. To our knowledge, this is the first study investigating activation of the CAIP using taVNS to potentially reduce symptoms of SIRS and alleviate intestinal failure as a motor of organ failure in a human model. By this pilot trial, we aim to provide a solid basis for further investigations of taVNS as a prophylactic tool in postoperative systemic inflammation and its associated organ failures.

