## Methods and analysis

### Sample size, recruitment, and blinding

The NeuroSIRS-Study is a prospective, randomized, two-armed, sham-controlled, double-blind, exploratory clinical trial in healthy subjects. It is a pilot study with the intention to gain first insights into the primary and secondary objectives. Therefore, sample size is not based on a statistical rationale. Thirty participants will be enrolled in the study: 15 subjects in the experimental group and 15 subjects in the control group. Healthy volunteers will be recruited by advertisements placed at the University Hospital of Bonn and in the local newspaper. During the screening visit, potential participants will be informed about the NeuroSIRS-Study. After sufficient time for consideration, a written informed consent will be obtained. Participants failing to meet inclusion criteria will not be enrolled in the study.

Since the NeuroSIRS-Study is an exploratory trial designed to give first insight into the impact on taVNS during systemic inflammation and to achieve the best possible comparability, it was decided to include only Caucasian men into the study. To ensure equal distribution of known and unknown variables between both groups, a randomization will be carried out upon enrolment. Patients are randomized to one of two therapy arms (arm A: taVNS application; arm B: sham stimulation/control). Randomization will be performed using central fax randomization according to a randomization list supplied by the Institute of Medical Biometrics, Informatics and Epidemiology, Study Center, University Hospital of Bonn. Participants and study personnel will be blinded until completion of the NeuroSIRS-Study. Application of the taVNS device will be carried out by study personnel. Stimulation settings (electrical stimulation or sham, i.e., no stimulation) will be adjusted by an independent physician who is otherwise not involved in the study. The stimulation settings will be concealed without the possibility for the investigator or the participant to see the settings.

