#### taVNS device

The tVNS®L device (Fig. 1) for taVN stimulation is provided by tVNS Technologies GmbH, Germany. Stimulation will be performed at 25 Hz, placing the auricular electrode upright in the left external ear. The left ear is chosen to avoid cardiac side effects and to increase outflow to the spleen, which is implicated in mediating the anti-inflammatory effects of VNS [37–39]. Intensity of stimulation will be increased until the participant describes a “tingling” sensation in the ear, without the sensation of pain. Usually, this tingling sensation is reached at 0.3–0.8 mA.

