#### Control group

taVNS electrodes are placed in the ear, but stimulation will not be started (sham stimulation). LPS will be administered the same way.

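### Participant blinding is not assured: active stimulation is titrated to tingling, sham delivers no current, and the article treats the problem as solved

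*Protocol article*

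**What the plan says.** The section on sample size, recruitment and blinding makes the claim without reservation: "Participants and study personnel will be blinded until completion of the NeuroSIRS-Study". An independent physician adjusts the settings, which are hidden from investigator and participant.

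The two arms differ in what the participant feels:

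- **Active arm.** The taVNS device section states "Intensity of stimulation will be increased until the participant describes a" tingling feeling, short of pain. The Discussion section on activation of the CAIP repeats the rule: "stimulation will commence at 0.1 mA and will be increased until the participant perceives a tingling sensation". It adds a further increase to find where the sensation becomes uncomfortable.
- **Sham arm.** The Control group section states "taVNS electrodes are placed in the ear, but stimulation will not be started (sham stimulation".

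The Limitations section describes tingling as a sensation "which is not felt during sham stimulation, leading to a potential unblinding during the trial". Its answer is "This problem will be solved during participant education", by mentioning that sensations may occur but need not.

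On who handles the device, the blinding section states "Application of the taVNS device will be carried out by study personnel". The Limitations section states that "randomization, setting, and placement of the electrode are performed by personnel not further involved in participant care or data extraction/analysis".

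**The concern.** Tingling is the required end point of titration in one arm and cannot come from the device in the other. Advice that sensations are optional leaves that difference in place. Hidden settings keep the display from staff and participant, but they do not hide what the participant feels.

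The conversation in which a participant is asked whether he feels tingling is a second cue, for whoever is present. The article describes no equivalent conversation for sham. Whether staff who must stay blinded are present depends on which of the two staffing statements is right.

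The primary objective is clinical symptoms of SIRS in the abstract and clinical signs of SIRS in the Objectives section. The symptom score in the Intervention section rests mostly on how a participant feels. If he believes he was treated, his ratings may shift without any anti-inflammatory effect. Paracetamol, available at any time for symptoms, is another route by which perceived allocation could reach the score.

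**Working it through.** The article states no figure on this point, and it says that the sample size has no statistical rationale. There is therefore no power calculation to reproduce. The check has four parts.

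**1. Composition of the score (Intervention section).** Headache, nausea, shivering, muscle pain and back pain are each rated 0 to 5, and vomiting adds 3.
- Maximum: 5 × 5 + 3 = 28, which agrees with the stated range.
- Pain items: 3 × 5 = 15 of 28.
- Pain plus nausea: 4 × 5 = 20 of 28.
- The other 8 points, shivering (5) and vomiting (3), are at least partly observable.

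The top anchor refers to the worst the person has ever experienced, which points to self-rating. The scorer is not named.

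**2. Timing.** Stimulation runs 30 min before and 60 min after LPS, 90 min in all. Scores are taken at 1 h and 1.5 h after stimulation starts, so one falls during stimulation and one at its end.

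**3. How well sensation predicts the arm.** Assume that every active participant feels tingling, that a share s of sham participants report some sensation anyway, and that each guesses active if he felt something. With equal arms, the share of correct guesses is (1 + (1 − s)) / 2.

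| s (assumed) | Correct guesses |
|---|---|
| 0% | 100% |
| 10% | 95% |
| 20% | 90% |
| 30% | 85% |
| 50% | 75% |

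Chance would give 50%.

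**4. What an expectation bias could do.** Inputs from the article are 15 per arm and group differences reported with 95% confidence limits. Assumptions are one comparison of a roughly normal summary of the score, equal SDs and no true effect.
- Half-width of the interval: t(0.975, 28) × √(2/15) = 2.048 × 0.365 = 0.748 SD.
- For a bias of b SD, the chance that the interval excludes zero in favour of taVNS is P(T > 2.048), where T is non-central t with 28 df and non-centrality b / √(2/15).

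| Bias b (SD, assumed) | Non-centrality | Chance that interval favours taVNS |
|---|---|---|
| 0 | 0 | 2.5% |
| 0.25 | 0.68 | 10% |
| 0.5 | 1.37 | 26% |
| 0.75 | 2.05 | 51% |
| 1.0 | 2.74 | 75% |

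The article gives neither the size of any expectation bias nor the SD of the score, so the table shows sensitivity and is not a forecast.

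**The case against.** The strongest reply is that the authors disclose the risk, that this is an exploratory pilot with a descriptive analysis, and that the independent physician and concealed settings protect the staff side. The groups are also parallel, so nobody can compare the two conditions. A sham participant told that sensations are optional need not conclude that he had sham, so the loss of blinding may be partial and heavier in the active arm. Much of this stands. It limits the size of the problem but does not justify calling it solved.

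Four stronger readings are tempting, and the article does not support them:

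- **That a self-rated score is the primary endpoint.** Self-rating is probable, but no section names the scorer or makes the 0–28 score the primary endpoint. The Discussion pairs the score with vital parameters and cytokines.
- **That the trial cannot separate expectation from effect at all.** Temperature, ECG, blood pressure, inflammatory mediators, capsule motility and the lactulose/mannitol ratio are all recorded and are less exposed. A symptom difference without support from them would itself suggest expectation.
- **That a bias of 0.75 SD would by itself produce an interval excluding zero.** That holds for an observed difference above the half-width of 0.748 SD. A true bias of 0.75 SD does so about half the time.
- **That no check of blinding exists.** The article mentions none, but it condenses a full protocol that is not shown. The point does not rest on that silence.

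Giving sham participants some current would change a no-stimulation control and would still leave a difference if tingling persisted only in the active arm. It is a design option and not an obvious correction.

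**Conclusion.** The concern holds for the blinding claim. By the article's own description, participants in the two arms have different sensory experiences, and the stated remedy does not remove the difference. Participant blinding is therefore not assured, and the statement that education solves the problem is wrong as written. The two accounts of who applies the device conflict and must be reconciled.

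The consequence is confined mainly to the symptom score. Expectation could contribute to an arm difference there. Assumed biases of 0.25 to 0.75 SD would raise the chance of an interval favouring taVNS from 2.5% to between about 10% and 51%. These figures rest on assumed biases, one comparison and no true effect. The article does not show that such a bias will occur.

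**What to change.** 1. Reconcile the blinding section with the Limitations section, so that only the independent physician or uninvolved personnel place the electrode and hold the setting conversation, away from anyone who scores symptoms.
2. At the end of stimulation, ask the participant and the symptom scorer to guess the arm. Report the guesses by arm with a blinding index. That moment is 60 min after LPS, before the symptom peak that the Discussion puts at about 2 h, so the guess is less coloured by how the participant fared. It cannot be recovered reliably later, and with 15 per arm the index will be imprecise.
3. Replace the statement that the problem will be solved with one saying that participant blinding is not assured.
4. Claim reduced SIRS only if the objective measures already collected support it. Otherwise report a symptom difference that may reflect expectation.

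Whether to use a sensation-matched sham, and with what settings, is for the investigators. The cost is one short form, a wording amendment and a more cautious claim.

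### Participant blinding is not assured: active current is raised to reported tingling, the sham is never switched on, and an information message cannot close that gap

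*Protocol article*

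**What the plan says.** All places are in the protocol article.

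- **Sample size, recruitment, and blinding:** "Participants and study personnel will be blinded until completion of the NeuroSIRS-Study". An independent physician adjusts the settings, which are hidden from investigator and participant.
- **taVNS device (active arm):** "Intensity of stimulation will be increased until the participant describes a" tingling feeling, short of pain.
- **taVNS for activation of the CAIP (active arm):** "stimulation will commence at 0.1 mA and will be increased until the participant perceives a tingling sensation". A second step follows: "Further increase of intensity will define the threshold when the sensation becomes discomforting". The working intensity is kept below that threshold.
- **Control group:** "taVNS electrodes are placed in the ear, but stimulation will not be started (sham stimulation").
- **Limitations of the NeuroSIRS-Study:** the section concedes that, for active treatment, "a tingling sensation at the outer ear is described, which is not felt during sham stimulation, leading to a potential unblinding during the trial". The remedy comes next: "This problem will be solved during participant education, mentioning that certain sensations might be felt intermediately but are not mandatory". The same paragraph adds that randomization, setting and electrode placement are done by people not otherwise involved in care or data handling.
- **Abstract and Primary objectives:** the primary objective concerns the clinical symptoms or signs of LPS-induced SIRS.
- **Intervention:** five flu-like symptoms are each scored 0 to 5, with 3 further points for vomiting, giving a total of 0 to 28. The upper anchor is the worst the person has ever had.

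**The concern.** The article identifies a threat to blinding, declares it solved, and keeps the participant-blinded claim. The declared solution does not act on the cause. Telling every man that sensations may or may not occur leaves the physical difference between the arms where it was: one arm has tingling that the man himself had to report, and the other has no current.

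The primary objective rests on symptoms such as headache, nausea and muscle pain, which are open to expectation. If active men believe they are being treated, they may rate symptoms lower whether or not the vagal pathway has been engaged. A symptom difference could not then be attributed cleanly to stimulation. This cannot be repaired after the data are collected.

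**Working it through.** The plan gives no figure for this point, and the sample size is declared to have no statistical rationale, so there is no planned number to reproduce. The check is a comparison of passages, followed by an illustration.

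**Step 1: what each arm can feel.**

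| | Active | Sham |
|---|---|---|
| Current | From 0.1 mA upward | None |
| Tingling | Reported by the man; it is the titration endpoint | Stated not to be felt |
| Discomfort threshold | Sought by a further increase | Cannot be reached without current |
| Duration | 30 min before LPS + 60 min after = 90 min | Electrode only |

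**Step 2: what each safeguard acts on.**

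- Hidden settings conceal the display, not the sensation.
- Separate personnel protect staff blinding, not the participant's.
- The education message reaches the participant, but it is the same for both arms and leaves the difference in sensation in place.

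No stated measure makes the two arms feel alike.

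**Step 3: link to the outcome.** The score has five symptoms of up to 5 points plus 3 for vomiting: 5 × 5 + 3 = 28. The upper anchor refers to the person's own past experience, which points to self-rating. Scores at 1 h and 1.5 h after the start of taVNS fall within, or at the end of, the 90 min of stimulation.

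**Step 4: illustration of size.** The only input from the documents is 15 men per arm. The documents give no SD and no size of expectation effect, so the shift b is an assumed range in SD units. The true effect is set to zero, and the interval is taken as a two-sample t interval.

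- Standard error of the difference: √(2/15) = 0.365 SD.
- 95% half-width: t(0.975, 28 df) × 0.365 = 2.048 × 0.365 = 0.748 SD.
- Chance that the estimate favours taVNS: Φ(b/0.365).
- Chance that the interval excludes zero in favour of taVNS: upper tail of the noncentral t with 28 df and noncentrality b/0.365.

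| Assumed shift b | b/0.365 | Estimate favours taVNS | Interval excludes zero in favour |
|---|---|---|---|
| 0 (no bias) | 0 | 50% | 2.5% |
| 0.3 SD | 0.82 | 79% | 12% |
| 0.5 SD | 1.37 | 91% | 26% |
| 0.8 SD | 2.19 | 99% | 56% |

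**The case against.** The other side has several fair points.

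- **Both arms unblinded.** A reader might infer that all 30 men will know their arm. The documents do not support that. Each man experiences one condition only, and a sham man told that sensations need not occur may stay unsure. The case is strong for active men and weaker for sham men. It is still enough to undercut the participant-blinded claim.
- **A dialogue in one arm only.** A reader might infer that only active men are questioned during intensity setting. The Control group section rules out current, not questions, and the full protocol may contain a sham script. What is established is a sensation in one arm only.
- **Internal contradiction.** The Discussion says: "It is hypothesized that a tingling sensation is necessary". A reader might set this against the message that sensations are not mandatory. The former is a physiological hypothesis and the latter is information given to participants, so they do not contradict each other.
- **Rater and endpoint.** The article does not say who does the scoring, nor does it name the 0–28 score as the primary endpoint. Both are inferences from the scale anchor and the primary objective. Staff can observe shivering and vomiting.
- **Exploratory pilot.** The analysis is descriptive and no hypothesis test is declared. Between-arm differences with 95% limits are still planned, and a descriptive label does not remove bias from them.
- **Already disclosed, with other outcomes alongside.** The authors raise the problem themselves, and the Discussion plans to use symptoms, vital parameters and cytokines together. This softens the consequence. It does not justify calling the problem solved.

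**Conclusion.** The concern stands in limited form. The statements that participants are blinded to completion and that education will solve the tingling problem are not supported by the design as described. Active men in particular can infer their arm, and a symptom difference could partly reflect expectation.

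The size of that bias is unknown. The 12%, 26% and 56% figures follow wholly from the assumed shifts of 0.3, 0.5 and 0.8 SD with no true effect and 15 per arm. They show how readily a trial of this size could be misled and do not forecast its result. Relevance to the primary objective rests on the inference that the symptom score is largely self-rated. Cytokines, temperature and capsule data are less exposed to expectation.

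**What to change.** 1. In Limitations of the NeuroSIRS-Study, replace the claim that education solves the problem with a statement that participant blinding is not assured. Qualify the participant-blinded claim in Sample size, recruitment, and blinding to match.
2. Reconcile taVNS device, Control group, taVNS for activation of the CAIP and Limitations on what men in each arm experience and are asked while intensity is set. Use the same scripted questions in both arms. This point does not ask for any current in the sham arm; that is for the investigators.
3. State who scores the symptoms. Just before LPS, before symptoms can inform the answer, record each participant's and each symptom scorer's guess of the arm, and report the guesses by arm.
4. Interpret the symptom difference beside those guesses and beside the less expectation-prone outcomes already collected: cytokines, temperature and capsule data.

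The cost is one question per person, some wording, and a less favourable blinding statement. These changes measure and disclose unblinding; they do not fully remove it.
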